**Fig. 1 Fig1:**
[figure not shown]
Participant flow diagram

An assessor from the research team will then contact potential participants via telephone to conduct the first component of the baseline assessment (T0) to confirm eligibility criteria and assess comorbidities. Potential participants deemed eligible except for current episode status/psychotic symptoms/active suicidality (see exclusion criteria below) will be offered a later assessment (one month following initial phone call) to determine eligibility at that time. Eligible participants will complete the second component of the baseline assessment (online questionnaires) (T0), followed by randomisation. An online coach will be assigned to the participant (contact initiated via a ‘welcome’ message). Participants will be asked to complete post-intervention (5-weeks, T1), 3-month (T2) and 6-month (T3) post-baseline assessments, involving a telephone interview and online questionnaires (see Table 1 for schedule of assessments). Participation in each assessment (phone and online components) will be compensated with USD$25 gift vouchers.

**Table 1 Tab1:** Schedule of assessments

Measure	Modality	T0 baseline	T1 (5 weeks post-baseline)	T2 (3 months post-baseline)	T3 (6 months post-baseline)
MINI Neuropsychiatric Interview (including Columbia Suicide Severity Rating Scale, C-SSRS)	Telephone	X	X	X	X
Brief Quality of Life in Bipolar Disorder (QoL.BD)	Online	X	X	X	X
Montgomery-Asberg Depression Rating Scale (MADRS)	Telephone	X	X	X	X
Young Mania Rating Scale (YMRS)	Telephone	X	X	X	X
Quick Inventory of Depressive Symptoms-Self Report (QIDS-SR)	Online	X	X	X	X
DASS-21 (anxiety and stress sub-scales)	Online	X	X	X	X
Functioning Assessment Short Test (FAST)	Telephone	X	X	X	X
Pittsburgh Sleep Quality Index (PSQI)	Online	X	X	X	X
Sleep, Circadian Rhythms and Mood questionnaire (SCRAM)	Online	X	X	X	X
Resource Use Questionnaire (RUQ)	Online	X		X	X
Assessment of Quality of Life-Eight Dimension (AQoL-8D)	Online	X	X	X	X
Five Facet Mindfulness Questionnaire (FFMQ)	Online	X	X	X	X
Self-Compassion Scale (SCS)	Online	X	X	X	X
Difficulties in Emotion Regulation Scale-16 item (DERS-16)	Online	X	X	X	X
Ruminative Response Scale-10 item (RRS-10)	Online	X	X	X	X
Responses to Positive Affect scale (RPA)	Online	X	X	X	X
Nonattachment to Self Scale	Online	X	X	X	X
Depressive Experience Questionnaire-Self Criticism Six-item Scale (DEQ-SC-6)	Online	X	X	X	X
Short Form of the Revised Almost Perfect Scale (SAPS)	Online	X	X	X	X
Medication adherence	Online	X	X	X	X
User feedback and engagement	Online and telephone		X	X	X
Reasons for withdrawal	Telephone		X	X	X

Assessors (masters-level in psychology) will be trained on study measures. Inter-rater reliability will be established for key observer-rated outcome measures (i.e. Montgomery-Asberg Depression Rating Scale, MADRS; Young Mania Rating Scale, YMRS), telephone assessment interviews will be recorded (except for participants who decline), and inter-rater checks will be conducted every three months. If rater drift is identified, assessors will be retrained.

### Strategies to maximise data quality

Online questions will be made mandatory where possible to reduce missing data. Comprehensive data cleaning (range and other distributional checks, comparison with published norms where relevant) will be conducted prior to analyses.

### Inclusion criteria

To ensure ready translation, minimally restrictive inclusion/exclusion criteria have been set. Inclusion criteria are as follows:Aged 18–65 yearsReceived a diagnosis of BD from a mental health professional (GP or Psychiatrist)Confirmation of DSM-IV diagnosis of BD as assessed by telephone interview with the M.I.N.I. International Neuropsychiatric Interview (MINI) [37]experienced 10 or more episodes of mania, hypomania or depression (assessed within the context of the MINI and assessor prompts, e.g., life events)under the care of a medical practitioner (at least one contact within the past 12 months) and able to provide contact details of local emergency servicesufficient understanding of written and spoken English to provide informed consent and engage with the interventionready daily access to the internet and adequate internet literacy

### Exclusion criteria

Exclusion criteria are as follows:experiencing a current episode of depression, hypomania or mania (assessed by MINI)currently psychotic (assessed by MINI)active suicidal ideation (assessed by Columbia Suicide Severity Rating Scale, C-SSRS) [38]

### Risk management

Risk management procedures have been developed through our experience with other online interventions and websites for BD [22, 39–43] and through consultation with the *CREST.BD* Community Advisory Group. Procedures pay particular attention to suicide risk, distinguish between solicited and spontaneously reported events, and are reviewed weekly during the trial by the study’s executive committee. To minimise impact of any adverse events, being under the care of a medical practitioner is an inclusion criterion, and participants consent to this professional potentially being contacted by the researchers as part of a ‘red flag decision tree’ (detailed below). The informed consent statement explains that the medical practitioner or local emergency department remains the participant’s first point of contact. Both the pre-registration page and informed consent statement highlight participants’ central role in their own safety and wellbeing, emphasising that the website does not act as an emergency service, and that the website is not monitored in real time. Links to emergency resources will be provided on the website (e.g., *unsuicide.**wikispaces.com*).

Participants will be withdrawn from the trial if their participation compromises clinical care as determined by the study’s executive committee. On a case-by-case basis, this might include hospital admission, acute hypomania or mania, psychotic symptoms or active suicidal intent.

Adverse events will be monitored via questions at post-test and both follow-up time points, and any adverse events incidentally reported through participant contact with coaches, forum posts, or assessments will also be recorded. Severity of any adverse events, and causal relationship to the trial will be assessed through participant self-report and logged. Adverse events will be reviewed at monthly executive meetings and 6-monthly meetings of the independent trial committee (who will also explore patterns of adverse events by condition). Serious adverse events suspected or known to be related to participation in the trial will be reported to Swinburne University of Technology Human Research Ethics Committee.

Clinical risks emerging will be addressed through a detailed ‘red flag decision tree’ which captures the various points at which the researchers could become aware of risk information (particularly suicidality), namely, baseline and follow-up (post-intervention, 3-month, 6-month) assessment interviews, posted comments on the website (e.g., forum content) and communications with the online coach (see below). Red flag events are those where there is immediate risk of harm (e.g., scoring high on suicide items, forum posts or coach emails suggesting active suicidality), as contrasted with other concerns highly prevalent in this population (e.g., comments about waxing and waning symptoms, connectedness or distress). Only in the former case have participants consented for researchers to break confidentiality and communicate with their clinician or emergency services, and these events are considered red flags for action of some kind. The decision tree distinguishes between red flag information suggesting immediate risk of harm for which real-time intervention is feasible/recommended (e.g., when active suicidality is identified during a phone assessment), and when it is not (e.g., when the research team becomes aware of active suicidality mentioned in a forum post from 48 h previous). All trial staff will be comprehensively trained on protocol procedures.

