## Method

This trial is conducted by an international multidisciplinary team of researchers and clinicians in Australia, Canada, USA and the UK. The study was reviewed and approved by Swinburne University of Technology Human Research Ethics Committee (2016/289). Trial objectives and protocol align with all aspects of Good Clinical Practice [34], the WHO Trial Registration Data Set (Version 1.2.1) and Standard Protocol Items: Recommendations for Interventional Trials (Additional file 1) guidelines [35]. The trial has been registered with ClinicalTrials.gov (NCT03197974). Any changes to this trial protocol will be described in this trial registry. Findings will be reported to the scientific community according to Consolidated Standards of Reporting Trials (CONSORT) eHEALTH criteria [36].

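### Participant self-report is the only stated method for judging severity and causality of adverse events, yet reporting of serious events to the ethics committee turns on relatedness

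*Protocol article*

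**What the plan says.** All the safety text cited here is in the protocol article, mostly under Risk management.

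- **Capture.** "Adverse events will be monitored via questions at post-test and both follow-up time points". In addition, "any adverse events incidentally reported through participant contact with coaches, forum posts, or assessments will also be recorded".
- **Judgement.** "Severity of any adverse events, and causal relationship to the trial will be assessed through participant self-report and logged".
- **Review.** "Adverse events will be reviewed at monthly executive meetings and 6-monthly meetings of the independent trial committee". The independent committee also looks for patterns by arm.
- **External reporting.** "Serious adverse events suspected or known to be related to participation in the trial will be reported" to the university ethics committee. The sentence does not say whose suspicion counts.
- **Immediate risk.** A separate decision tree, operated by the research team, covers urgent cases: "Red flag events are those where there is immediate risk of harm".

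Two later sections bear on the point. Statistical analysis of primary outcome leaves two groups out of the effort to follow everyone up: those who choose to leave, and those withdrawn on ethical grounds. Other outcome measures and mechanism variables provides for a short phone call to participants who ask to leave, at which adverse events are documented.

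**The concern.** The judgement sentence states a method; it does not merely leave one out. Relatedness decides whether a serious event goes to the ethics committee, and the participant's own account is the only stated way of establishing relatedness.

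That method is weakest for the events that matter most in this population. Risk management gives admission to hospital, mania or hypomania, psychosis and suicidal intent as possible grounds for withdrawing someone. A person in one of these states may be unable to say whether the programme contributed, or may say so unreliably. After a death, or when contact is lost, no account can be obtained.

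At stake is whether a serious event that the trial may have caused reaches the ethics committee.

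**Working it through.** No arithmetic applies. The article states no rate of serious events and no share of events without a usable self-report. The check sets the sections side by side.

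**Step 1. Is anyone other than the participant named as judge of severity or causality?** No.
- Risk management names only self-report.
- The two committees review events, but neither is said to assign severity or relatedness.
- The decision tree acts on immediate risk of harm and is not said to assign causality.
- Under Secondary outcome measures and in Table 1, the MINI, with the C-SSRS, is given at every assessment. It detects episodes and suicidality and does not attribute them.

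**Step 2. Does anything turn on the causality judgement?** Yes. Ethics reporting is limited to serious events for which relatedness is suspected or known. Committee review carries no such condition. The dependence is therefore confined to the ethics route.

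**Step 3. Which participants have a stated route to a causality rating?**

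| Participant | Stated route | Self-report available? |
|---|---|---|
| Remains in follow-up and is well enough to answer | Questions at post-test, 3 months and 6 months | Yes |
| Asks to leave | Phone call about reasons, adverse events documented | Probably |
| Withdrawn by the executive committee on ethical grounds | Excepted from the follow-up effort; the phone call is described only for those who ask to leave | None stated |
| Acutely manic, psychotic, suicidal or in hospital | Scheduled questions, if reached | May be absent or unreliable |
| Unreachable | Incidental report only | May be absent |
| Deceased | None | No |

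The third row matters most. The grounds for withdrawal that Risk management offers as examples are themselves serious psychiatric events. The rule on follow-up then removes these participants from the effort that would have put the adverse event questions to them. Table 1 has a telephone row for reasons for withdrawal, but the text describing that item covers only participants who request to stop.

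**Step 4. What happens to an event with no usable self-report?** If the team learns of it, it is logged and seen by both committees. No rule says how its relation to the trial is decided or whether it goes to the ethics committee.

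**The case against.** The strongest reply is that the reporting sentence does not tie suspicion to the participant. Committee review is placed between the judgement sentence and the reporting sentence, and either committee could form its own suspicion. This stands. A reader might infer that the participant's attribution alone decides whether an event is reported, but that would be an inference from silence. What can be said is that self-report is the only basis the text gives.

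The second reply is that events do not disappear. This also stands. Adverse events go to both committees with no relatedness filter, so the independent committee already receives them whatever the attribution. Its comparison by arm needs no individual causality rating. Detection has other routes as well: coach contact, forum posts, the decision tree, assessor interviews at each time point, and a relapse measure that counts hospitalisation and emergency visits for new mood symptoms. A reader might infer that serious events go unrecorded or that the trial's account of harm would be understated. The documents support neither.

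Third, a reader might set the judgement sentence against the statement under Method that "Trial objectives and protocol align with all aspects of Good Clinical Practice". The documents do not set out what that standard requires for causality assessment, so they show no contradiction.

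Fourth, this is a condensed article, and a full protocol might name an adjudicator. That limits how firmly the gap can be asserted. It does not remove it, because the published sentence assigns the judgement to self-report and does not leave it open.

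Finally, severity is not seriousness, and nothing says that participants decide whether an event is serious.

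**Conclusion.** The point holds in a limited form. Severity and causal relationship are to be assessed through participant self-report, with no other judge named, and ethics reporting of serious events depends on relatedness. For participants who are acutely unwell, in hospital, out of contact, deceased or withdrawn on ethical grounds, that report may be missing or unreliable. A related serious event may then fail to reach the ethics committee, although both trial committees would still review it once it is known.

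The size cannot be calculated from the article. The 33% attrition figure should not be used for it: that is a sample-size allowance for the primary outcome at 5 weeks, not a rate of serious events that cannot be assessed.

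The conclusion assumes that no document outside the article names another assessor of relatedness. If the full protocol does so, the remaining task is to bring the published sentence into line with it. Limiting ethics reporting to related serious events is not itself an error. The weakness lies in how relatedness is judged. The change is worth making because it is cheap and concerns safety oversight.

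**What to change.** Amend the judgement sentence under Risk management in three respects:

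1. Participant self-report is recorded as one input to the assessment of severity and relatedness.
2. A clinically qualified member of the executive committee, who is neither a coach nor an outcome assessor, assigns both at the existing monthly meetings. Excluding coaches keeps the judgement away from those delivering the intervention. Excluding outcome assessors helps keep them unaware of allocation.
3. A serious event with no usable self-report, including one in a participant who has been withdrawn, cannot be reached or has died, is judged by the same person. If its relation to the trial cannot be excluded, it is treated as suspected related for ethics reporting.

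Nothing needs to change in what the independent committee receives. The cost is protocol wording, slightly more classification work at meetings that already take place, and a few more reports to the ethics committee.

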### Intervention content

To minimise attrition and non-adherence the intervention is brief, with a 5-week structured participation time, with each new module released sequentially. Participants will complete modules at their own pace: content within modules is organised into ‘chunks’ allowing exploration in briefer or longer individual sessions, depending on personal preferences. Suggested guidelines on using the program to maximise benefit will be provided, including spending a minimum of 1–2 h each week on content and ongoing skills-practice (with daily practice recommended for mindfulness skills and mood monitoring).

Both interventions comprise four modules, with new module content delivered sequentially each week over four weeks. The fifth week is positioned as an opportunity to consolidate skill development. Participants can return to previous modules across the program at any time. To support ongoing generalisation of skills, participants retain access to the program for the 6-month follow-up period.

To maximise engagement, the interventions follow best practice in persuasive system design. Features known to impact engagement are included: (1) *dialogue support* (praise from coach and forum moderator, email reminders), (2) *social support* (social facilitation through discussion threads in moderated forums) and (3) *primary task support* (best practice principles for modularisation of content, personalisation/monitoring of progress, prompted self-monitoring, and rehearsal) [44]. Website presenters include experienced clinical academics and consumers with lived experience of BD. Topics within modules are organised primarily around videos (2–3 min in length), followed by text, reflective exercises, audio exercises and additional information PDFs. Participants can comment publically on videos (via comments feed) and complete exercises which are private but can be shared with others users of the website.

Coaching support improves adherence to web interventions [40]. Both interventions therefore include personal coaching support through asynchronous email contact with a trained online coach. Participants can send as many messages as they like to their coach, and will receive one response per week. Completed activities can be shared with the coach to facilitate skill development. A moderated forum is included to develop a sense of online community. The forum is moderated by trained consumers with lived experience of BD, who will also seed discussion threads with encouraging tips.

#### Mindfulness for bipolar 2.0

This is a bespoke web-based intervention tightly targeted at QoL outcomes in late stage BD. Intervention content is framed around the development of five overlapping skills: Mindfulness (self-awareness, mindfulness as a tool for emotion regulation), Values and Committed Action (identifying personal values as a guide to action), Acceptance (of negative experiences, contrasted with struggling), Defusion (creating distance from unproductive thoughts, emotions and sensations), and Self-compassion (cultivating self-compassion in the context of ongoing symptoms and previous disappointments).

Content draws from best-practice psychological interventions of potential utility in BD, specifically ACT, MBCT and CFT [45]. To support generalisation to real world settings and maintenance upon completion of the 5-week active phase, classical principles of behaviour change (as commonly used, for example, in Cognitive Behavioural Therapy) are applied. Website aesthetics, structure and navigation are informed by our previous experience, particularly development of a web-based intervention for people with serious mental disorder [46].

Intervention content is well suited to web delivery, using multi-media tools (video, audio, downloadable information sheets, etc.) to introduce skills that participants can practice experientially with well-planned exercises. Real-world application of skills is emphasised throughout, and facilitated through online and downloadable goal-setting and monitoring tools.

#### Psychoeducation for bipolar

Psychoeducation is a meaningful comparator given that it is beneficial as an adjunctive treatment for BD and is readily translated into web format [47]. The active control condition here, Psychoeducation for Bipolar, is a 5-week, web-based guided self-help intervention informed by the approach of Colom and Vieta [48]. Material is organised into four modules (*Bipolar and You, Treatments, Knowing the Signs,* and *Staying Well*), with a focus on factual information about BD including available medications and treatments, skill development (mood monitoring, recognising triggers and early warning signs) and strategies to stay well (lifestyle factors, coping behaviours, crisis planning).

### Outcome measurements

The schedule of assessments is provided in Table 1. Assessments are performed as close as practicable to specified time points. All clinician-rated assessments are conducted by telephone by expertly trained assessors, unaware of treatment allocation. All self-report assessments are completed online via a secure, encrypted online survey platform (Qualtrics). Participants are contacted via email to arrange a time for phone assessments and to prompt completion of online assessments. If an email response is not received within two days, an SMS reminder is sent to the participant. Assessors will monitor the completion of questionnaires on a regular basis and make telephone calls to facilitate completion where such support may be required. The MINI is conducted via telephone at baseline to confirm eligibility, establish comorbid diagnoses and record demographic variables.

#### Primary outcome measure

The primary outcome, QoL, will be measured at T1 using the total score of the Brief QoL.BD [33]. This measure was developed specifically for repeated measures use, assessing 12 factor-analytically derived domains (Physical, Sleep, Mood, Cognition, Leisure, Social, Spirituality, Finance, Household, Self-esteem, Independence, and Identity) from the parent instrument (the 56-item Qol.BD). The parent instrument has demonstrated strong effect size associations with objective measures of functioning [49], generic QoL measures [33], and BD-linked cognitive processes [50]. In the validation sample (*N* = 224 patients), Cronbach’s α for the 12 items of the Brief QoL.BD was 0.87, and standard deviation of total scores was 8.76, giving a reliable change on the Brief QoL.BD of 3.16 points [33]. Sensitivity analysis found the 12-item Brief QoL.BD had superior sensitivity to change in clinician-rated symptoms than commonly used generic QoL measures. Brief QoL.BD scores have been shown to be sensitive to intervention effects in two published RCTs [22, 51], and the measure has been validated for online use.

